## Abstract

**Methods and analysis::**

We designed a prospective observational single-center study. Four groups of 30 patients will be studied: group 1, including insulin-requiring type 2 diabetic patients undergoing on-pump CABG; group 2, including non-insulin-requiring type 2 diabetic patients undergoing on-pump CABG; group 3, including non-diabetic patients undergoing aortic SVR; and group 4, including non-diabetic patient undergoing on-pump CABG. Preoperative (baseline) and postoperative BG variability will be quantified using the Abbott’s Freestyle Libre Pro sensor allowing for continuous subcutaneous BG monitoring. Preoperative (baseline) and postoperative ANS activity will be measured using noninvasive continuous heart rate monitoring (Mooky HR memory®). Blood level and urinary concentration of inflammatory and endothelial dysfunction biomarkers will be measured from blood and urinary samples at the end of the surgery and on postoperative day 1 and 2. The primary objective is to describe the relationship between baseline BG variability and postoperative BG variability. The secondary objectives are to describe the relationship: between baseline and postoperative BG variability according to the diabetes phenotype and to the type of surgery; between the ANS activity and the BG variability; and between postoperative BG variability and, urinary and blood biomarkers.

## 1. Introduction

Blood glucose (BG) variability in diabetic and non-diabetic patients is independently associated with increased morbidity and mortality in the intensive care unit and after cardiac events.^[1–3]^ In cardiac surgery patients, BG variability is reported to be associated with severe postoperative complications – leading to an increase length of intensive care unit (ICU) stay – regardless of the quality of BG control obtained during the perioperative period.^[4–6]^

Several hypotheses have been raised to explain the deleterious effect of BG variability observed in diabetic patients. Basal state BG variability seems to depend on the diabetes phenotype and to differ between people with or without diabetes.^[7,8]^ Furthermore, some studies suggest an association between BG variability and the activity of the autonomic nervous system (ANS).^[9–13]^ Finally, other studies highlight that the deleterious effect of BG variability includes increased oxidative stress, endothelial dysfunction, and cell apoptosis.^[14–16]^ However, no study has specifically addressed this issue in cardiac surgery patients and the underlying mechanisms contributing to increased perioperative BG variability and to its deleterious impact remain unclear.

The aim of this study is to investigate whether postoperative GV could be related to preoperative GV and/or to perioperative alteration of the ANS activity in diabetic and non-diabetic cardiac surgery patients and the relationship between postoperative GV and blood and urinary level of inflammation and endothelial dysfunction biomarkers.

## 2. Objectives

The primary objective is to describe the relationship between baseline (preoperative) and postoperative BG variability within 48 hours after surgery.

Secondary objectives are: to describe the relationship between baseline and postoperative BG variability within 48 hours after surgery according to the diabetic status and to the type of surgery; to describe the relationship between the preoperative activity of the ANS and the baseline BG variability; to describe the relationship between the preoperative activity of the ANS and the postoperative BG variability within 48 hours after surgery; to describe the relationship between postoperative BG variability within 48 hours after surgery and the postoperative activity of the ANS within 48 hours after surgery; to describe the relationship between postoperative BG variability within 48 hours after surgery and the diabetes phenotype; to describe the relationship between postoperative BG variability within 48 hours after surgery and the urinary and blood level of biomarkers of inflammation and of endothelial dysfunction; and to describe the morbidity and the mortality within 30 days after surgery.

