The MooKy HR memory® sensor will be temporarily removed during the surgery to allow the access to the surgical site. Then, the MooKy HR memory® sensor will be applied on the chest wall after admission in the ICU up to 48 hours after surgery. The postoperative activity of the ANS will be measured using the MooKy HR memory® using the same heart rate variability metrics as preoperatively. All heart rate and invasive arterial pressure values collected during the first 48 hours using the standard monitoring will be extracted from the Carescape B850 monitor and stored on a dedicated computer. The analysis of the data collected using the aHRV Analysis software (Nevrokard Izola, Slovenia) will allow the measurement of the postoperative activity of the ANS by calculating the following parameters: the standard deviation of the NN intervals (SDNN), the standard deviation of the average NN intervals for each 5 minutes segment of a 24 hours recording (SDANN), the percentage of successive RR intervals that differ by more than 50 ms (pNN50), the LF, the HF, the LF/HF and the RMSSD. SDNN, SDANN and pNN50 are indicators of the global activity of the ANS. Morever, the aHRV Analysis software (Nevrokard Izola, Slovenia) will allow to quantify the activity of the baroreflex by combining the temporal trend of the heart rate and of the invasive arterial pressure values collected using the Carescape B850 monitor within 48 hours after surgery.

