### 3.8. Outcome measures

The primary outcome will be the mean difference between the preoperative (baseline) and the postoperative CV, and its 95% confidence interval, measured using the subcutaneous glucose sensor Abbott® Free Style Libre Pro.

Secondary outcomes will: the preoperative and postoperative BG variability, quantified by the preoperative and postoperative values of: the SD of BG, the CV, the MAGE, the glycemic lability index and the glycemic penalty index; the preoperative and postoperative activity of the ANS, quantified by the preoperative and postoperative values of: the COMPASS 31 score, the LF, the HF, the LF/HF ratio, the RMSSD, the SDNN, the SDANN, and the pNN50; the diabetes phenotype, described by the preoperative fasting BG and glycosylated hemoglobin values; the blood and urinary levels of biomarkers of inflammation (IL^-^2, IL^-^6, IL^-^10, TNF^-^alpha, 8^-^iso^-^prostanglandin^-^F_2*α*_) and of endothelial function [Endocan, angiopoietin^-^1 (Ang^-^1), angiopoietin^-^2 (Ang^-^2), vascular endothelial (VE)^-^cadherin]; and postoperative morbidity and mortality at day 30 after surgery. Postoperative morbidity includes cardiac arrest, stroke, cardiac arrhythmia requiring therapeutic intervention, surgical wound infection, pneumonia, renal failure requiring dialysis, sepsis, surgical revision, readmission in the intensive care unit or in hospital.

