### 3.12. Statistical analysis

Categorical variables will be compared using the Chi^-^square test or Fisher’s exact test. Normally distributed quantitative variables will be compared using the Student *t* test or an analysis of variance (ANOVA). Non^-^normally distributed quantitative variables will be analyzed using the non^-^parametric Wilcoxon or Kruskall^-^Wallis tests. Statistical tests for repeated measures will be used for before^-^ after comparisons (paired Student *t* test or paired Wilcoxon test, 1^-^way ANOVA with repeated measures or Friedman test).

The primary outcome will be described using the mean and the 95% confidence interval of the mean. The temporal trend of preoperative, intraoperative, and postoperative BG variability will be described by the mean and the 95% confidence interval of the mean of each variable describing BG variability and figured as boxplot. The relationship between preoperative and postoperative BG variability, between BG variability and the ANS activity and between the postoperative BG variability and the blood and urinary level of biomarkers of inflammation and endothelial function will be investigated using the Pearson or the Spearman correlation coefficient and univariate linear regression models and presented on adequate figures.

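### The aim asks about perioperative alteration of ANS activity, but the plan relates BG variability only to the preoperative or the postoperative ANS level, one at a time, so a perioperative change cannot be separated from a pre-existing difference

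*Protocol article*

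**What the plan says.** The Introduction gives the aim as finding out "whether postoperative GV could be related to preoperative GV and/or to perioperative alteration of the ANS activity in diabetic and non-diabetic cardiac surgery patients".

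Section 2 has three objectives on ANS activity. One sets preoperative ANS against baseline BG variability. The second is "the relationship between the preoperative activity of the ANS and the postoperative BG variability within 48 hours after surgery". The third takes postoperative BG variability "and the postoperative activity of the ANS within 48 hours after surgery".

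Section 3.8 lists "the preoperative and postoperative activity of the ANS, quantified by the preoperative and postoperative values of" the COMPASS 31 score and the heart rate variability metrics. It defines no change or difference for any of them.

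Section 3.12 investigates the links between BG variability and ANS activity "using the Pearson or the Spearman correlation coefficient and univariate linear regression models". It also plans paired tests for before-after comparisons in general.

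Section 3.7 records LF, HF, LF/HF and RMSSD on a chest sensor from the day before surgery, then again in the ICU for up to 48 hours "using the same heart rate variability metrics as preoperatively".

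**The concern.** Read in its ordinary sense, a perioperative alteration is a change within the patient around surgery. Every ANS objective uses a level at one time point, and a one-predictor regression cannot hold the preoperative and postoperative values together.

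Patients who differ in ANS activity before surgery may still differ afterwards. If the preoperative difference goes with BG variability, the postoperative level will also correlate with it, even when what happened to the ANS around surgery has no bearing on glucose. A reader guided by the aim could then take the 48-hour correlation as support for the perioperative explanation. What is at stake is how one secondary result is interpreted. The primary outcome and the sample size are not affected.

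**Working it through.** **1. The text side by side.**

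| Place | ANS quantity | Linked to BG variability? |
|---|---|---|
| Introduction, aim | perioperative alteration | yes, postoperative |
| Section 2 | preoperative level | yes, baseline |
| Section 2 | preoperative level | yes, postoperative |
| Section 2 | postoperative level | yes, postoperative |
| Section 3.8 | pre- and postoperative values, no change defined | not applicable |
| Section 3.12, association | one predictor at a time | yes |
| Section 3.12, paired tests | average before-after shift | no |

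The quantity in the first row does not return in any later row that is linked to BG variability. The paired tests can show that ANS activity moves on average, but not that patients who move more have more variable glucose.

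**2. The plan's own figure.** Section 3.11 gives SD 8.2, a 95% interval no wider than 6.12 and 30 patients per group. Width = 2 × t(0.975; 29) × 8.2/√30 = 2 × 2.045 × 8.2/5.477 = 6.124, which agrees after rounding. The illustration below uses the total, n = 120.

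**3. Illustration.** All correlations are assumed; the documents give none. Let a be the correlation of preoperative ANS with postoperative BG variability, and r the correlation of preoperative with postoperative ANS. The change itself is unrelated to BG variability.

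- Unadjusted correlation of postoperative ANS with BG variability: ρ = a × r.
- Partial correlation given preoperative ANS: (a·r − a·r)/√((1 − a²)(1 − r²)) = 0.
- Chance of p < 0.05, by the Fisher z approximation: Φ(√(n − 3) × atanh ρ − 1.96), with √117 = 10.82.

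| a | r | ρ | √117 × atanh ρ | Chance of p < 0.05 |
|---|---|---|---|---|
| 0.3 | 0.4 | 0.12 | 1.304 | Φ(−0.656) = 0.26 |
| 0.4 | 0.6 | 0.24 | 2.648 | Φ(0.688) = 0.75 |
| 0.5 | 0.7 | 0.35 | 3.953 | Φ(1.993) = 0.98 |

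Simulation gives the same range, 25% to 98%. A wider grid (a from 0.2 to 0.5, r from 0.3 to 0.7; 20,000 simulated studies per setting) gives 9% to 98% at n = 120 and 6% to 48% within one group of 30. With the preoperative value in the model, rejection is about 5% in every setting.

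**4. Why not a raw change score.** With equal variances before and after, the correlation of (post − pre) with BG variability is −a × √((1 − r)/2). For a = 0.4 and r = 0.5 this is −0.4 × 0.5 = −0.20, although the change has no bearing on glucose. Across the wider grid at n = 120 it is significant in 13% to 91% of studies.

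**5. Measurement error.** Now assume BG variability correlates 0.4 with a stable true ANS level. Each recording adds error (reliability 0.6 or 0.8), and an unrelated perioperative shift has half the variance of a preoperative reading. At n = 120 the unadjusted postoperative analysis is significant in 80% (reliability 0.6) and 90% (0.8) of studies. Adjustment for the measured preoperative value leaves 27% and 15%. In this model the raw change score stays near 5%, because the stable level is carried through surgery in full. Under the assumptions of steps 3 and 4 it is not, and there the change score misleads.

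**The case against.** The strongest reply is that the mismatch turns on one word. Section 3.7 describes a higher COMPASS 31 score as a more severe alteration of the ANS, which is impairment at a single time point. Read that way, the aim is about impaired ANS activity around surgery, and the pre- and postoperative objectives cover it. This reading is possible, so it is not established that a stated hypothesis goes wholly untested. It does not dispose of the point: the postoperative level still carries whatever was there before surgery, so it cannot show that an impairment arose perioperatively.

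The objectives are also descriptive and the study is observational. A real postoperative correlation would answer the third objective correctly as written. That stands. The problem arises only when the correlation is read as an answer to the aim.

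A reader might infer that a lifelong autonomic difference will be reported as an effect of surgery. The documents support neither part: baseline ANS is measured the day before surgery, so only *pre-existing* can be said, and the objectives speak of relationships. Nor do they support the inference that the postoperative correlation mostly repeats the preoperative one. The assumed r of 0.4 to 0.7 means a shared variance of only 16% to 49%, and the repetition appears because the illustration sets the contribution of the change to zero.

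Finally, covariates for secondary analyses are often left to a SAP, which is not shown. That carries limited weight here, because the objectives belong in the protocol and section 3.12 itself fixes one-predictor models.

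**Conclusion.** The point holds in a limited form. As written, the plan cannot separate a perioperative change in ANS activity from a pre-existing difference when it relates ANS to postoperative BG variability. The paired tests do not fill the gap.

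The figures of about 25% to 98% unadjusted, against about 5% adjusted, show that the mechanism can matter at n = 120. They are not a forecast: they rest on assumed correlations, on no contribution of the change, and on ANS measured without error. With weaker assumed correlations the unadjusted figure falls to 9%. With assumed reliability of 0.8 to 0.6, about 15% to 27% false positives remain after adjustment. It is a worthwhile correction to a secondary analysis.

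**What to change.** If a change within the patient was meant:

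- Add an ANS-alteration objective to section 2 and its model to section 3.12. For each of LF, HF, LF/HF and RMSSD, regress postoperative BG variability on the postoperative value, adjusted for the preoperative value of the same metric. Take both values from the chest sensor, since section 3.7 also derives these metrics postoperatively from the bedside monitor.
- Do not use a raw change score for this purpose.
- Keep the level-only correlations as description.
- State that adjustment is incomplete if ANS is measured with error.

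If impairment at a time point was meant, reword the aim in the Introduction to pre- and postoperative ANS activity, and do not interpret the postoperative correlation as evidence of a perioperative change.

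The cost is wording plus one covariate that is already planned for collection. Patients without a usable preoperative recording drop out of this model. The sample size stays as it is, because it rests on the precision of the CV difference.

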## 3. Methods and analysis

This manuscript is written in accordance with the SPIRIT guidelines for the reporting of interventional trial protocols.^[17]^

### 3.1. Trial design

This is a prospective observational single center study.

### 3.2. Eligibility

Adult patients who undergo planned on-pump coronary artery bypass surgery or aortic valve replacement surgery in the University Hospital of Besancon, France (Centre Hospitalier Universitaire (CHU) de Besancon) will be eligible for inclusion.

Four groups of 30 patients will be studied: group 1, including insulin-requiring type 2 diabetic patients undergoing on-pump coronary artery bypass graft (CABG); group 2, including non-insulin-requiring type 2 diabetic patients undergoing on-pump CABG; group 3, including non-diabetic patients undergoing aortic surgical valve replacement; and group 4, including non-diabetic patient undergoing on-pump CABG.

Inclusion and exclusion criteria for the present study are listed below.

### 3.3. Inclusion criteria

Signed informed consent.Planned on-pump CABG or aortic valve replacement surgery (see above).Patient affiliated to French Social Security or equivalent.Ability to speak, write and understand French language.

### 3.4. Exclusion *criteria*

Emergent surgery defined by a surgery performed < 48 hours after the anesthesia consultation.Combined surgery (coronary artery bypass combined with valve surgery, multiple valve replacement, ascending aorta surgery).Off-pump CABG.Type 1 diabetes mellitus.Chronic preoperative heart rhythm disorder (regular extrasystoles, chronic atrial fibrillation).Pacemaker dependence.Body mass index < 18 kg m^–2^ or >35 kg m^–2^.Age under 18 years or over 80 years.Pregnant or breast^-^feeding women.Expected life expectancy < 48 hours.Legal incapacity or limited legal capacity.Subjects without health insurance.Subjects within the exclusion period of another study.

### 3.5. Study procedure and patient management

Eligible patients will be screened and informed during the anesthesia consultation. Written informed consent will be obtained the same day by investigators after an oral explanation of the study.

After inclusion in the study, patient characteristics, past medical history including ASA physical status and Euroscore value, and preoperative fasting BG and glycosylated hemoglobin values will be collected.

All patients will be admitted to the Cardiac Surgery Department the day before surgery. All patients included in the study will be managed according to the current practices for the management of patients undergoing planned cardiac surgery. Briefly, on arrival in the operating room, standard monitoring (Carescape B850 monitor, General Electric Healthcare, USA) will be set up. A dedicated peripheral venous catheter will be inserted in a forearm vein to infuse anesthetic drugs. All patients will receive manually driven target^-^controlled infusion of propofol and remifentanil to maintain bispectral index (BIS) values between 40 and 60. All patients will be paralyzed using non depolarizing neuromuscular blocking agent (either cisatracurium or atracurium). After induction of anesthesia, patients will be intubated, and tidal volume and respiratory rate will be set to maintain the end^-^tidal carbon dioxide between 35 and 40 mm Hg. Inspired oxygen fraction will be adjusted to obtain a pulse oximetry ≥ 95%. A central venous catheter inserted in the internal jugular vein, a urinary catheter and an indwelling arterial catheter introduced in a radial artery will be implemented. No intravenous glucose will be administered intraoperatively in the absence of hypoglycemia (defined as <75 mg/dL [4.1 mmol/L]). Tranexamic acid (1.5 g before incision and 1.0 g before surgical wound closure) and antibiotic prophylaxis with cefuroxime (1.50 g before skin incision, reinjection at priming of the extracorporeal circulation and then 0.75 g every 2 h until end of surgery) or linezolid 600 mg in case of allergy to cefuroxime will be initiated before incision.

Intraoperative data describing the surgical procedure and the anesthetic management will be obtained from the computerized anesthesia monitoring sheet: type and duration of surgery; duration of aortic cross clamping; duration of extracorporeal circulation; intraoperative blood loss and urine output; intraoperative blood transfusion and total volume of fluids infused.

At the end of surgery, all patients will be admitted to the intensive care unit (ICU) and will stay during at least the first 48 postoperative hours, and then will be discharged to the ward. During the ICU stay, all patients will undergo the same standard monitoring (Carescape B850 monitor, General Electric Healthcare, USA) as in the operating room, that is the continuous monitoring of at least heart rate, electrocardiogram, pulse oximetry and invasive arterial pressure. Sedation will be stopped, and the patients will be extubated as soon as possible according to the usual criteria (i.e., free of sedation, normothermic, fulfilling specified respiratory criteria). Postoperative analgesia will consist in intravenous paracetamol 15 mg/kg 4 times a day and patient^-^controlled analgesia with morphine. Intravenous glucose infusion will be administered at a constant rate of 4.0 to 4.5 g/hours until oral feeding could be resumed and at least during the first 48 postoperative hours. BG control will be managed according to a validated and published dynamic insulin therapy protocol,^[18]^ adapted from Goldberg *et al*^[19]^ and implemented in our ICU since December 2005. Briefly, hourly BG measurement starts with the skin incision. All BG values are obtained, from glucose meter readings (Optium Xceed; Abbott Diabetes Care, UK) measured from arterial blood samples taken from the arterial line. The target BG level is 100 to 139 mg/dL (5.5–7.7 mmol/L). Intravenous insulin infusion starts with the first BG value > 139 mg/dl (7.7 mmol/L). After an initial bolus of insulin based on the BG value, the infusion rate is adjusted based on 3 parameters: the current BG value; the previous BG value; and the current insulin infusion rate. When hypoglycemia occurs, the insulin infusion is stopped and intravenous dextrose 30% is administered (10 mL if BG is between 50 and 74 mg/dL [2.7–4.1 mmol/L] and the patient is asymptomatic; 20 mL if BG is between 50 and 74 mg/dL [2.7–4.1 mmol/L] and the patient is symptomatic or if BG is <50 mg/dL [<2.7 mmol/L]). The insulin infusion is resumed 1 hour after the first BG value > 100 mg/dL (>5.5 mmol/L) at a lower rate (75% of the original rate if BG is between 50 and 74 mg/dL [2.7–4.1 mmol/L] and 50% of the original rate if BG is <50 mg/dL [<2.7 mmol/L]). Depending on the patient’s clinical condition, oral intakes are initiated as soon as possible, and the intravenous insulin infusion is replaced by subcutaneous insulin when necessary.

Post^-^operative morbidity including major adverse events (MAEs) (cardiac arrest, stroke, cardiac arrhythmia requiring therapeutic intervention, surgical wound infection, pneumonia, renal failure requiring dialysis, sepsis, surgical revision, readmission in the intensive care unit or in hospital) and post^-^operative mortality will be assessed on day 30 after surgery.

All data will be collected using the Clean Web web^-^based system (Telemedicine Technologies, France).

